### Analyses

#### Power analysis

Sample size calculations were performed using the STATA package ‘clustersampsi’ [44]. The control mean loneliness score was assumed to be 49 (*SD* = 10), and intervention mean of 45 (*SD* = 10), based on findings reported across similar samples [45, 46] and indicators of significant and clinically meaningful change across more diverse samples [47]. Intra Cluster Correlation was assumed conservatively to be 0.05. It was calculated that 13 clusters per arm, with 20 participants recruited per cluster, would have 81% power and 5% type 1 error rate to detect a difference in loneliness at 6 months of 4 points. A retention rate of 70% was assumed based on the research team’s track record of achieving excellent follow-up rates across similar samples [48, 49].

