#### Data analysis

Statistical analyses will be managed by independent statisticians. Loneliness scores will be analyzed using linear regression in a mixed modelling framework. Fixed effects will include terms for intervention, time point (7 weeks or 6 months), an interaction between intervention and time point, baseline loneliness score, and strata (community-based vs. residential), and random effects for cluster and participant will be included to account for clustering by site, and repeated measurements on participants. The estimated mean difference in loneliness scores between the arms at the primary (6 months) and secondary (7 weeks) time points will be reported, along with 95% confidence intervals, and p-values, as summary measures of the intervention effectiveness.

The analysis set for the primary outcome will be Intention to Treat, however, sensitivity analyses using the Per Protocol analysis set will also be performed. In the case of missing data, multiple imputation methods will be utilized to ensure the analysis set is Intention to Treat. Analysis of secondary outcomes at 7 weeks and 6 months will also utilize linear mixed models (if assumptions of normally distributed residuals and constant variance are met) or generalized linear mixed models otherwise. Fixed effects will include those listed above for the primary outcome variable. Effect estimates for the difference between arms, 95% confidence intervals, and p-values, will be reported for each outcome at each follow-up time point. A sub-group analysis will be performed estimating the difference in change in loneliness from baseline among those participants who reported high loneliness scores at baseline. A secondary sub-group analysis comparing the difference in loneliness scores at 7 weeks and 6 months for residential participants compared to community-based participants will also be performed.

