### Strengths and limitations

The study poses various strengths, particularly its focus on the “real world”, by aiming to examine the effectiveness of a loneliness intervention when implemented in routine care across AOD treatment services. Since the research closely aligns with real clinical practice, it will provide reliable information about the effectiveness of the group-based loneliness intervention when embedded into routine care. The study also aims to improve the generalizability of the findings by minimizing exclusion criteria. Additionally, having assessment officers who are blind to treatment conditions collect primary and secondary outcomes helps reduce bias and enhance the validity of the findings. Finally, the study has been designed to accurately monitor aspects of intervention fidelity (e.g., training and support of clinicians, monitoring delivery of the intervention) to maximize the confidence in findings of the trial.

Potential challenges may include the prospect of a low recruitment rate and/or high participant attrition. To maximize recruitment, a desire to improve social connections has been specified as an eligibility criterion, rather than loneliness, since there may be some reluctance to disclose feelings of loneliness throughout the recruitment process (due to social stigma associated with loneliness, e.g., [16]) and there is an established high prevalence of loneliness across similar samples [3]. Sub-group statistical analyses will help to account for this as a potential limitation. Additionally, the power analyses have adopted a conservative approach to ensure sufficient power. The study team has demonstrated a strong track record of successfully recruiting both services and participants for similar studies. To further safeguard these potential limitations, the research team includes both advisors with lived experience and representatives from key non-government AOD treatment providers to support recruitment and site retention. Additionally, to facilitate participant retention and minimize drop out, multiple strategies will be used, including remuneration for participation, obtaining detailed contact information, and identifying multiple secondary contacts.

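### The only analysis by baseline loneliness is confined to high scorers, so it cannot show whether the effect varies with baseline loneliness or is diluted by less lonely entrants

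*Protocol article*

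**What the plan says.** In the protocol article, Strengths and limitations explains that eligibility rests on wanting better social connections and not on loneliness, so some entrants may not be very lonely. It then says of this choice: "Sub-group statistical analyses will help to account for this as a potential limitation".

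Data analysis describes the primary model. It is a linear mixed model for the loneliness score at 7 weeks and 6 months, with intervention, time point, their interaction, baseline loneliness and service-type stratum as fixed effects, and random effects for cluster and participant. Baseline loneliness enters as a covariate only.

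The same section then lists two sub-group analyses. The first is "estimating the difference in change in loneliness from baseline among those participants who reported high loneliness scores at baseline". It names no time point, and nothing is said about participants below the high range. The second is "comparing the difference in loneliness scores at 7 weeks and 6 months for residential participants compared to community-based participants", which is a comparison between two groups.

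**The concern.** The limitation that the authors name is one of mixture. If the programme helps lonely people and does little for others, enrolling both pulls the overall effect down. Finding out whether that happened means comparing the effect at higher and lower baseline loneliness. The stated analysis looks at one end only.

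A significant result among high scorers is compatible with the same effect in everyone else. A null result there is compatible with no effect anywhere, or simply with a smaller sample. Either could be reported as the programme working, or not working, in lonely people in particular, without that having been examined.

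The wording also moves from a baseline-adjusted follow-up score to change from baseline. If the sub-group estimate and the overall estimate differ, part of the gap could come from the method.

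**Working it through.** **1. The plan's own figure.** Inputs from Power analysis: means 49 and 45 (difference 4), SD 10; "Intra Cluster Correlation was assumed conservatively to be 0.05"; "13 clusters per arm, with 20 participants recruited per cluster"; "A retention rate of 70% was assumed". A two-sided test is assumed, as sidedness is not stated.

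- Analysed per cluster: m = 20 × 0.70 = 14, so 13 × 14 = 182 per arm.
- Design effect: 1 + (14 − 1) × 0.05 = 1.65. Effective n per arm: 182 / 1.65 = 110.3.
- SE of the arm difference: 10 × √(2 / 110.3) = 1.347.
- Power for 4 points (non-central t, 24 df): 81.3%.

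The stated 81% reproduces. It refers to the overall comparison at 6 months; the article states no power for any sub-group.

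**2. What one stratum can and cannot show.** Suppose, purely for illustration, that half the participants score high and the true effect in that half is 4 points.

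- If the effect in the other half is also 4, the overall effect is 0.5 × 4 + 0.5 × 4 = 4: no dilution.
- If the effect in the other half is 0, the overall effect is 0.5 × 4 + 0.5 × 0 = 2: the effect is halved by dilution.

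The stratum estimate targets 4 in both cases, so it cannot tell them apart.

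**3. Precision of the stratum estimate.** The share of high scorers is not in the article, so 30%, 50% and 70% are assumed. SD 10 and ICC 0.05 are kept, and no gain from baseline adjustment is taken. SE = 10 × √(2 × DE / (13 × m)), with DE = 1 + (m − 1) × 0.05.

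| Share high | m per cluster | DE | SE | Power for 4 points (24 df) |
|---|---|---|---|---|
| 30% | 4.2 | 1.16 | 2.06 | 46% |
| 50% | 7.0 | 1.30 | 1.69 | 62% |
| 70% | 9.8 | 1.44 | 1.50 | 72% |

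**4. Precision of the contrast.** For a high-versus-low difference in effect, assume that the cluster effect is common to both groups within a site and cancels. The within-cluster variance is 100 × 0.95 = 95, and SE = √[(2 × 95 / 13) × (1/m_high + 1/m_low)].

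- 50% high: √[14.615 × (1/7 + 1/7)] = 2.04. Power for a 4-point interaction: Φ(4/2.04 − 1.96) ≈ 50%. Detectable with 80% power: 2.802 × 2.043 ≈ 5.7 points.
- 30% or 70% high: √[14.615 × (1/4.2 + 1/9.8)] = 2.23. Power ≈ 43%. Detectable with 80% power: 2.802 × 2.23 ≈ 6.25 points.

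These are high/low figures. The continuous term proposed below was not calculated separately, because its precision depends on the spread of baseline scores, which the article does not give.

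**The case against.** The strongest reply is that the article never asks whether the effect depends on baseline loneliness. It admits people who may not be lonely, and it plans an estimate in those who are. That is a legitimate descriptive quantity, and this much stands. But the article presents sub-group analysis as the answer to a limitation that exists only because lonely and less lonely people are analysed together, and one stratum answers only half of that. Setting the stratum result beside the overall result does not close the gap. The two share participants, may be on different scales, and come with no interval for their difference.

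A second reply is that the change wording is loose. It most naturally means a between-arm difference in change, so regression to the mean does not bias it. If baseline stays in the model as a covariate, modelling change or follow-up score gives the same arm estimate. That is correct, so the point on scale is one of consistency. A reader might infer a sizeable loss of efficiency, but the article gives no baseline to follow-up correlation and does not say that baseline adjustment is dropped.

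Three further readings are tempting and not supported:

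- That the cut-off for high will be chosen after seeing the data. It may be fixed in the statistical analysis plan, which is not shown; its absence from an article is no fault.
- That this is the trial's key sub-group analysis. The article does not rank it so.
- That the residential versus community analysis has the same defect. It is already worded as a comparison.

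**Conclusion.** The point holds as one about the choice of analysis. As written, the analysis by baseline loneliness yields the effect among high scorers and nothing about how the effect changes across the baseline range, so it only partly serves the purpose given in Strengths and limitations. It should be changed, but the primary analysis does not depend on it.

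Its size cannot be fixed from the article. The 62% power is an illustration under an assumed 50% share and no baseline adjustment. It should not be read as a shortfall against the 81%, which was claimed only for the whole sample. Low power is also not the main argument, since the contrast recommended here is itself imprecise. What the contrast adds is a direct estimate of the quantity in question, with an interval that shows how little or how much the data can say.

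**What to change.** In the primary mixed model, add intervention × baseline UCLA score (continuous), with its interaction by time point. Report the interaction with its 95% confidence interval, and the model-based arm difference at 6 months at baseline scores named in advance. Label the analysis exploratory. This also gives the effect in lonely participants, so it can replace the single-stratum estimate. If a high-loneliness estimate is kept as well, obtain it from the same baseline-adjusted model. State that a result in that group alone will not be read as evidence that the effect differs by baseline loneliness.

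The cost is wording and a few model terms; no new data or participants are needed. Because multiple imputation is planned, the imputation model should allow for the same interaction. There are two drawbacks. The interaction will probably have a wide interval, so a null must not be reported as proof of a uniform effect. The single term also assumes that the effect changes linearly with baseline score, which should be stated and checked.

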### Economic analysis plan

A trial-based economic evaluation will be conducted from a health system perspective based on Intention to Treat. Resource use data associated with participation in the intervention, and treatment as usual will be prospectively identified, measured, and valued. Outcomes included in the analysis will be aligned to the primary trial outcome – incremental change in loneliness as well as change in health-related quality of life, measured using the AQoL-8D [31] to be transformed into incremental Quality Adjusted Life Years. Incremental cost-effectiveness ratios (ICERs) will be calculated by dividing the between-group difference in costs by the between-group difference in effects. Uncertainty intervals around the ICERs will be estimated using non-parametric bootstrapping techniques and graphically presented on cost-effectiveness planes. Acceptability curves and net monetary benefit will also be calculated. Sensitivity analysis will test for variability in parameters such as unit costs and event likelihood. The analysis will incorporate results from the CSRI, to capture patterns of downstream service use and associated costs. Given the expected longer-term impact of improving mental wellbeing among this population, a lifetime model will be specified and populated to understand the longer-term value of *Groups for Belonging*.

### Qualitative study

In the treatment arm, participants who attend *Groups for Belonging* (anticipated *N* = 30, depending on point of saturation), and service staff who co-facilitate *Groups for Belonging* (i.e., research staff and clinicians employed at sites, *N* = 10), will be interviewed about their experience of the program and asked to reflect on the key aspects of *Groups for Belonging* (treatment processes and content) that they perceive contribute to belonging. The interviews will be conducted following the completion of the *Groups for Belonging* program. Qualitative interview data in the treatment arm will be generated to understand barriers and facilitators surrounding the implementation of *Groups for Belonging*, and perceived mechanisms by which the program may work to reduce loneliness.

Demographic and descriptive information will be synthesized using descriptive statistics. Qualitative zoom interviews will be audio recorded (with prior consent from participants) and sent for transcription by a professional transcriber working under a confidentiality agreement. Data coding and analyses will be guided by iterative categorization. Iterative categorization is compatible with common analytical approaches (e.g. thematic analysis) and offers a clear, standardized guide for coding which allows for replication and validity in qualitative data analysis [50].

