### Conditions

#### Treatment condition (Groups for belonging and TAU)

Participants allocated to the treatment condition will complete treatment as usual in addition to completing Groups for Belonging [17]. Groups for Belonging involves 6 × 2-hour sessions (*n* = approximately 10 participants per group) delivered over a 4 to 6-week period, depending on the length of the program offered by respective treatment sites (i.e., up to 2 sessions can be delivered per week where necessary). *Groups for Belonging* is based on cognitive theories of loneliness, which posit that unhelpful cognitions act as barriers to connection [14], and a social identity approach which suggests that identification with social groups enhances connection and belonging [18, 19]. The program aims to help participants understand the connection between loneliness and substance use, identify relationships that might be barriers or facilitators to their AOD treatment goals, to identify and manage the cognitions (e.g., stigma, mistrust, fear of negative evaluation, fear of showing feelings) that act as barriers to connection, and to develop goals and strategies that help to promote positive social connections. Figure 2 outlines the key aspects of the *Groups for Belonging* program.

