### Follow-up

Follow-up will be conducted via telephone at 7-weeks after baseline and again at 6-months post-intervention. To ensure blind assessment of outcome measures, the primary and secondary dependent measures will be collected by an assessment officer who is naïve to allocation and study design. At the beginning of each phone call, participants will be reminded that they should not reveal their condition to the assessment officer. If participants disclose their condition, an alternative assessment officer will complete the assessment. Assessments will take approximately 30 min to complete. Multiple methods will be used to stay in contact with participants (e.g. telephone, email, SMS, social media). Alternate contact details provided by the participant will be used if there is difficulty reaching the participant. Table 1 reflects a schedule of assessments, including the primary and secondary outcomes collected at each time point.

**Table 1 Tab1:** Schedule of assessments

Domain	Data		Assessment Interval			
		Pre-Trial	Baseline	Intervention period	7-w	6-m
Recruitment	Eligibility	x ^c^				
Demographics						
	Date of Birth		x^b^			
	Age		x^b^			
	Postcode		X^b^		x^a^	x^a^
	Gender		X^b^			
	Aboriginal and/or Torres Strait Islander		x^b^			
	Marital status		x^b^			
	Sexual orientation		x^b^			
	Dependents/children		x^b^			
	Living arrangements		x^b^			
	Accommodation		x^b^			
	Education		x^b^			
	Employment		x^b^			x^a^
	Job status		x^b^			
	Previous treatment episode		x^b^			
	Mental health diagnoses		x^b^			
	Physical health conditions		x^b^			
	Medications		x^b^			x^a^
Substance use						
	TLFB (i.e. days of use)^2^		x^a^		x^a^	x^a^
	Treatment goals		x^b^		x^a^	x^a^
	Cravings (DAQ-6)^2^		x^a^		x^a^	x^a^
Loneliness						
	Single item		x^b^			
	Drinking Motivations		x^b^			
	UCLA (Version 3)^1^		x^a^		x^a^	x^a^
Social variables						
	Multiple group membership^2^		x^a^		x^a^	x^a^
	SEMSI		x^b^		x^a^	x^a^
	Use/recovery identity		x^b^		x^a^	x^a^
	Support for treatment goals		x^b^		x^a^	x^a^
Barriers to connecting						
	Self-stigma		x^b^		x^a^	x^a^
	Mini-SPIN		x^b^		x^a^	x^a^
	Young Schema Questionnaire (mistrust, emotional inhibition, defectiveness/shame)		x^b^		x^a^	x^a^
Wellbeing						
	Psychological health (K10)^2^		x^a^		x^a^	x^a^
	Suicidality (CSSRS-S)		x^a^		x ^a^	x ^a^
	Quality of life (AQoL-8D)^2^		x^a^			x^a^
Experience of Care						
	YES				x^a^	
	PREMAT				x^a^	
Service use						
	CSRI^2^		x^a^			x^a^
	Travel^2^		x^b^	x^c^	x^a^	

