### Experience sub-study

During the consultation with service providers in the development of the research protocol, it was identified that services providers in the control condition would value the collection of satisfaction and experience measures to help inform continuous service improvement following the completion of the formal RCT. Subsequently, a mixed methods sub study was developed that is focused on understanding the experience of treatment for people accessing treatment as usual. Satisfaction and experience measures have been embedded in the protocol (i.e. YES survey and PREMAT) to provide a mechanism to examine the relationship between satisfaction and experience with outcomes. Likewise, in the control arm, consumers (anticipated *N* = 30) and service staff members (anticipated *N* = 10) will be interviewed about their experience of care in accessing (consumers) or delivering (staff) treatment. The interviews will be conducted either in person (where possible) or online following the 7-week assessment timepoint (consumers) or following consent procedures (staff). Qualitative interview data in the control arm will be generated to examine factors that consumers and service staff perceive as effective or ineffective. This will cover aspects of the facility, program elements, and interactions with both staff and other consumers at the service they are using.

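### Interview timing differs by arm: treatment participants may be interviewed about belonging before their 7-week loneliness score, control consumers may not (minor)

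*Protocol article*

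**What the plan says.** All references are to the protocol article.

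- **Qualitative study (treatment arm).** Participants who attended the groups are interviewed; the expected number is "30, depending on point of saturation". They are asked about the aspects of the program "that they perceive contribute to belonging". On timing the section says "The interviews will be conducted following the completion of the" Groups for Belonging program, and nothing more.
- **Experience sub-study (control arm).** The number is similar: "consumers (anticipated *N* = 30". These interviews have a different anchor: they take place "following the 7-week assessment timepoint (consumers"; staff have a separate rule).
- **Conditions, Treatment condition.** The six sessions are "delivered over a 4 to 6-week period, depending on the length of the program offered by respective treatment sites".
- **Follow-up.** "Follow-up will be conducted via telephone at 7-weeks after baseline and again at 6-months post-intervention".
- **Data analysis.** The arm difference in loneliness is estimated at 6 months (primary) and at 7 weeks (secondary). Each is reported with a 95% confidence interval and a p-value. The model contains an intervention-by-time interaction.

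**The concern.** The two arms have different rules for when a participant may be interviewed relative to the first outcome assessment. A control consumer cannot be interviewed before the 7-week call. A treatment participant can be, if the program has finished by then.

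The treatment-arm interview asks people to think about what in the program helped them to belong. That is close to what the UCLA Loneliness Scale measures by self-report. A reflective interview shortly before the scale could move the answers, and only in one arm. The direction is uncertain: it could reinforce a sense of connection or bring its absence to mind.

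What is at stake is the secondary 7-week loneliness difference, together with the other measures taken at week 7. These include psychological distress, cravings and the two experience-of-care surveys in both arms, and the group climate and program evaluation items in the treatment arm.

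**Working it through.** **1. Can the interview come before the assessment?** Let *s* be the number of weeks from baseline to the first session, and *L* the length of the program (4 to 6 weeks, Treatment condition section). The program ends at week *s* + *L* after baseline. The assessment is at week 7 after baseline (Follow-up section). The window for an earlier interview is therefore 7 − (*s* + *L*) weeks. The article does not give *s*, so I show a range of assumed values.

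| *s* (assumed) | *L* = 4 | *L* = 6 |
|---|---|---|
| 0 weeks | 3 weeks | 1 week |
| 1 week | 2 weeks | none |
| 3 weeks | none | none |

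The window exists with a prompt start and closes with a late one. The Design and Data collection sections describe the 7-week visit as post-intervention, so the schedule itself expects the program to be over by about then.

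**2. The plan's own power figure, to obtain a standard error.** Inputs from the Power analysis section: SD 10, difference 4, ICC 0.05, 13 clusters per arm, 20 recruited per cluster, 70% retention.

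- Analyzed per cluster: 20 × 0.70 = 14. Per arm: 13 × 14 = 182.
- Design effect: 1 + (14 − 1) × 0.05 = 1.65.
- Effective n per arm: 182 / 1.65 = 110.3.
- SE of the difference: 10 × √(2 / 110.3) = 1.35.
- Power, noncentral t with 2 × (13 − 1) = 24 df, two-sided 5%: 81.3%, which agrees with the stated 81%.

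This SE belongs to the 6-month planning assumptions and is not adjusted for baseline score. I use it only as a yardstick at 7 weeks.

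**3. Upper bound on the share of the arm affected.** Suppose all 30 interviews come before the 7-week assessment.

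- Of those recruited: 30 / 260 = 11.5%.
- Of those retained, if all 30 are among them: 30 / 182 = 16.5%.

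**4. Upper bound on the shift.** Shift = δ × 30 / n, where δ is the effect of one interview on the UCLA score. The documents give no value for δ, so the values below are assumptions.

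| δ (points) | n = 260 | n = 182 | Share of 4 points (n = 182) | In SE units (n = 182) |
|---|---|---|---|---|
| 1 | 0.12 | 0.16 | 4% | 0.12 |
| 2 | 0.23 | 0.33 | 8% | 0.24 |
| 4 | 0.46 | 0.66 | 16% | 0.49 |

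The last row is extreme: it supposes that one interview has as large an effect as the whole intervention is planned to have. The 4-point benchmark was set for 6 months and is used here only for scale.

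**The case against.** The best case against the point is that the article contains no contradiction. An interview held after week 7 complies fully with the Qualitative study section, and control participants have no program completion date, so a different anchor for them is natural. Exact scheduling of a sub-study could also sit in a fuller protocol. Part of this stands: early interviews are permitted, not planned. But this is more than a missing detail. The article states a timing rule for each arm, and the rules differ in a way that matters for a tested comparison.

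Three stronger readings are tempting, and the documents do not support them.

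- *Treatment interviews take place in weeks 4 to 6, before the assessment.* The 4 to 6 weeks is the delivery period and runs from the first session, whereas the 7 weeks runs from baseline. With the gap between them unknown, some groups may finish at or after week 7.
- *The interviews threaten the blinding.* Treatment participants already know their arm from attending the groups, and nothing says that assessment officers conduct the interviews. The Follow-up section has participants reminded at each call not to reveal their condition, and another officer takes over if they do. No added risk is shown.
- *The primary result is biased because both time points share one model.* The intervention-by-time interaction gives each time point its own arm difference. The 7-week scores bear on the 6-month estimate mainly through participants with missing 6-month data, which dilutes an already small shift. By 6 months, about 30 participants in each arm may have been interviewed, so the one-sidedness has largely gone.

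**Conclusion.** The point holds as a minor one. The stated rules allow a one-sided measurement influence at week 7 without requiring it. It could reach at most about 11.5% to 16.5% of the treatment arm and, under an assumed interview effect of 1 to 4 points of uncertain direction, shift the 7-week loneliness difference by at most about 0.16 to 0.66 points, or 0.12 to 0.49 standard errors.

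These bounds assume that all 30 interviews come first and that all 30 interviewees are among the 182 retained; any departure from either makes the shift smaller. The size of an interview effect cannot be learned from the documents. The point is worth acting on because the asymmetry is avoidable and precedes a comparison reported with a p-value.

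**What to change.** In the Qualitative study section, state that each treatment-arm participant is interviewed only after that participant's own 7-week assessment is complete, which is the anchor the Experience sub-study section already uses for control consumers. Interviews with staff who co-facilitate the groups need no change.

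The cost is one sentence and a scheduling check for about 30 interviews. Some will be held later than they could have been, by at most 3 weeks if a 4-week program starts at baseline and the assessment takes place on time, with slightly older recall of the program. Sample size, power, intervention and analysis model are unchanged.
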